**Methods:**

VISION, a 24-week, phase 4, prospective, randomized, multicenter, open-label, parallel-group study, will include 3312 Chinese T2DM patients aged ≥18 years who are inadequately controlled (6.5% >HbA1c ≤9%) by metformin (750–1000 mg/day). Eligible patients will be randomized to receive either vildagliptin plus metformin or up-titration of metformin monotherapy (5:1). Patients will also be subgrouped (1:1:1:1) based on their age and body mass index (BMI): <60 years and <24 kg/m^2^; <60 years and ≥24 kg/m^2^; ≥60 years and <24 kg/m^2^; and ≥60 years and ≥24 kg/m^2^.

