**Figure 1 F1:**
[figure not shown]
Design of the VISION study.

Patients participating in the study will be subgrouped (1:1:1:1) based on their BMI and age into 4 groups: (1) <60 years and BMI <24 kg/m^2^; (2) <60 years of age and BMI ≥24 kg/m^2^; (3) ≥60 years of age and BMI <24 kg/m^2^; and (4) ≥60 years of age and BMI ≥24 kg/m^2^. In each group, patients will be randomized according to the study design. At visit 1, patients meeting the inclusion criteria will be assigned to open-label metformin 500 mg bid for a 4-week lead-in period. At visit 2, patients will be randomized in a ratio of 5:1 to receive either vildagliptin 50 mg bid plus metformin 500 mg bid (Group A) or metformin 500 mg tid (Group B) for the next 4 weeks. From visit 3 to the end of the study, Group A patients will continue to receive the maintenance dose of vildagliptin 50 mg bid plus metformin 500 mg bid, while group B patients will receive metformin 1000 mg bid.

The primary, secondary, and exploratory objectives of the study are shown in Table 2. The study drug will be discontinued if it shows unsatisfactory efficacy at week 12 (i.e., FPG >13.3 mmol/L [240 mg/dL]) confirmed by a repeated measurement in the absence of any concurrent illness. Worsening of glucose levels in the absence of any other explainable concurrent disease or emergency condition that can affect glucose levels, the occurrence of AEs including GI side effects or clinically significant changes in laboratory parameters, or an abnormality that, in the opinion of the investigators, requires immediate withdrawal of treatment, will also lead to the study drug being discontinued. An inexplicable increase in levels of liver enzymes (aspartate transaminase, alanine aminotransferase and total bilirubin) without any clinical signs that is confirmed by a repeat measurement within 3 working days, pregnancy, severe or frequent hypoglycemia (i.e., unexplained hypoglycemic events requiring the assistance of another person or >3 hypoglycemic events within a week), treatment with prohibited concomitant medications, or any other deviation from the treatment protocol will also lead to treatment discontinuation. The reason for a patient discontinuing treatment will be recorded in the case report form.

**Table 2 T2:** Primary, secondary, and exploratory objectives of the VISION study

	
**1.**	**Primary objective:**

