### Data analysis

Intention-to-treat (ITT) analysis will be performed. The full analysis set (FAS) will include all randomized patients who took the study drugs at least once and had at least 1 primary or secondary efficacy evaluation after baseline. For assessment of missing primary efficacy variables, the last observation carried forward (LOCF) technique will be used. The per-protocol set (PPS) will include ITT patients completing at least 22 weeks of treatment, and those who discontinued the study due to a poor therapeutic response (FPG >13.3 mmol/L [240 mg/dL]) after 12 weeks of treatment, provided they have no major protocol deviations and had a valid assessment of HbA1c levels within 7 days after their last dose of study drug. Any major deviation from the protocol will be identified and documented in the analysis plan. Patients will be analyzed in the treatment group to which they were randomly assigned for the efficacy assessment.

The safety analysis set (SAS) will include patients who took the study drugs at least once and had at least 1 safety assessment after baseline. The safety analyses will be according to the patients’ treatment, and will include the description of any AEs.

The FAS set will be used as the primary population for the primary efficacy variable, the change from baseline in HbA1c levels at 24 weeks. The primary efficacy variable will be analyzed using an analysis of covariance (ANCOVA) model and the LOCF approach.

Non-inferiority of the study drug will be analyzed using the null hypothesis and a unilateral alternative hypothesis, which are defined as follows:

$$H_{0},\delta_{\mathrm{vildagliptin}}\geq \delta_{\mathrm{metformin}}+0.3\%$$

$$H_{a},\delta_{\mathrm{vildagliptin}}<\delta_{\mathrm{metformin}}+0.3\%$$

where δ represents the change from baseline.

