### Sample size estimations

Non-inferiority testing will be performed on the subgroups of patients based on age and BMI. Assuming a treatment group difference of 0, standard deviation of 1, and a non-inferiority margin of 0.5, 690 patients will provide 90% power at a 1-sided with significance level of 0.05. Allowing for a 20% dropout rate, the number of subjects required for randomization is 690/ (1+20%) = 828 patients, yielding a total of 4 × 828 = 3312 subjects. For the estimation of the sample size, nQuery Advisor®, version 7.0, will be used.

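### The dropout step behind 828 per subgroup is false as printed, and 828 covers 16.7% dropout rather than 20%; at a 0.3% margin this costs about one point of subgroup power

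*Protocol article*

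**What the plan says.** The Sample size estimations section of the protocol article sizes the trial for non-inferiority within each of the four age/BMI subgroups. Its inputs are: "Assuming a treatment group difference of 0, standard deviation of 1, and a non-inferiority margin of 0.5". From these it says that "690 patients will provide 90% power at a 1-sided with significance level of 0.05". It then allows for 20% dropout and concludes that "the number of subjects required for randomization is 690/ (1+20%) = 828 patients". Four such subgroups give 3312, and the Abstract repeats that total: the study "will include 3312 Chinese T2DM patients".

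Three statements elsewhere bear on the check:

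- The hypotheses in Data analysis use a margin of 0.3%, not 0.5.
- Under Study design, "At visit 2, patients will be randomized in a ratio of 5:1".
- Data analysis makes the full analysis set (FAS) primary, with last observation carried forward (LOCF). The per-protocol set serves as the robustness analysis.

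**The concern.** The one calculation displayed for the sample size does not give the number printed beside it. The slash and the plus sign are both legible, so a reader who checks the line gets 575.

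Two single-character corrections suggest themselves, and neither rescues the claim. If the slash should be a multiplication sign, the line balances, but adding 20% to 690 does not leave 690 after 20% are lost. If the plus should be a minus, the method is right but the answer is no longer 828. Either way, the stated dropout allowance and the stated number to randomise do not belong together, and 3312 is built on that number.

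At stake are the accuracy of the stated 20% allowance and the 90% power claimed for each subgroup.

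**Working it through.** **Inputs.** From Sample size estimations: 690 per subgroup, difference 0, SD 1, one-sided alpha 0.05, power 90%, dropout 20%, margin 0.5. From Data analysis: margin 0.3%. From Study design: 5:1 allocation.

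**Step 1: reproduce 690.** With allocation r = 5, the metformin arm needs n = (z₀.₉₅ + z₀.₉₀)² × SD² × (1 + 1/r) / margin², where (1.645 + 1.282)² ≈ 8.56.

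| Margin | Metformin | Vildagliptin | Subgroup total |
|---|---|---|---|
| 0.3 | 8.56 × 1.2 / 0.09 ≈ 114.2, so 115 | 575 | 690 |
| 0.5 | 8.56 × 1.2 / 0.25 ≈ 41.1, so 42 | 210 | 252 |

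The 690 follows exactly from 0.3 and not from the printed 0.5.

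**Step 2: the printed dropout step.**
- As printed: 690/(1 + 0.20) = 575.
- What gives 828: 690 × 1.20 = 828. Then 4 × 828 = 3312, which is correct multiplication.
- What leaves 690 after 20% loss: 690/(1 − 0.20) = 862.5, so 863 per subgroup and 4 × 863 = 3452 in total.
- Shortfall: 863 − 828 = 35 per subgroup and 3452 − 3312 = 140 overall, about 4%.

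**Step 3: what 828 supports.**
- Largest dropout that leaves 690: 1 − 690/828 = 16.7%.
- Remaining after 20% complete loss: 828 × 0.80 = 662.4, about 662, split about 552 to 110.

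**Step 4: subgroup power.** Power = Φ(margin / (SD × √(1/n₁ + 1/n₂)) − 1.645), one-sided alpha 0.05, 5:1.

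For 662.4 patients, √(1/552 + 1/110.4) ≈ 0.1043. At margin 0.3, 0.3/0.1043 − 1.645 ≈ 1.23, and Φ(1.23) ≈ 0.891.

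| Evaluable per subgroup | Margin 0.3 | Margin 0.5 |
|---|---|---|
| 690 | 90.2% | 99.9% |
| 662 | 89.1% | 99.9% |

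The noncentral t gives 90.1% and 89.0% in the margin 0.3 column.

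**Step 5: overall test.** Four subgroups of 662.4 give about 2650 patients. The standard error is half the subgroup value, about 0.0521, and 0.3/0.0521 − 1.645 ≈ 4.1. Power is above 99.9%.

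**The case against.** A reader might infer that 828 per subgroup fails to deliver the planned 90% power, or that the trial is underpowered. The documents do not support that, for four reasons.

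1. **The margin.** On the sample size paragraph's own margin of 0.5, 662 patients give about 99.9% power. The 89% figure appears only when the 0.3% of the hypotheses is used. That is very probably the planning margin, since it reproduces 690, but the paragraph does not say so. The power statement must therefore be conditional.
2. **The analysis set.** The 662 assumes that every dropout vanishes from the analysis. The FAS needs one dose and one post-baseline efficacy evaluation. HbA1c is measured at week 12, and the final-visit assessments are also required at early withdrawal (Table 3, footnote a). At 20% dropout about 166 of 828 leave; if about 28 of them (one in six) contribute data, 690 are analysed and the shortfall is gone. So 662 is the worst case for the FAS at that dropout rate. It is a more natural figure for the per-protocol set, which mostly requires 22 weeks of treatment.
3. **The objective.** The primary test is the overall comparison and comes first in the sequence. The 690 and 828 serve the subgroup tests, which Table 2 lists as secondary.
4. **The size.** Even at 0.3% with complete loss, the effect is about one percentage point.

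All four points stand, and they limit the consequence. They do not repair the equation, and they do not turn a 16.7% allowance into 20%. The plan chose to inflate for a 20% loss, and on that premise 828 is not the number that results. That the slash may be a misprint for a multiplication sign is plausible, since 828 and 3312 agree with each other and with the Abstract, but the inflation would still be the wrong one.

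**Conclusion.** The printed equation is wrong, and the inflation actually used is not the one that preserves 690 after 20% dropout. The stated 828 per subgroup covers 16.7% dropout; a strict 20% allowance would be 863 per subgroup and 3452 in total.

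The consequence is small: subgroup power of about 89% instead of 90%. This rests on a margin of 0.3%, SD 1, true difference 0, 5:1 allocation, one-sided alpha 0.05 for each subgroup test, and complete loss of 20% of patients from the analysis. At a margin of 0.5 subgroup power stays at about 99.9%. The overall primary test is not materially affected under either margin.

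This is a correction to a stated figure and its justification, not a case for recruiting more patients. The conflict between 0.5 and 0.3% in the same calculation is the larger inconsistency, and it has to be settled before any power figure can be restated.

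**What to change.** Keep 3312. Remove the printed division and replace it with wording such as: *690 × 1.2 = 828 per subgroup, which allows for 16.7% dropout; if 20% are lost from the analysis, about 662 remain, with about 89% power per subgroup at a margin of 0.3%.* Add that this figure concerns the secondary subgroup tests, not the overall primary test.

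In the same edit, reconcile the 0.5 margin in Sample size estimations with the 0.3% margin in Data analysis. Without that, a sentence giving 89% power would stand beside a margin at which power is 99.9%, and so add a new error.

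The cost is a few words of text and a slightly less favourable stated figure. No patients are added and trial conduct does not change.

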### Ethics

The design, implementation, and reporting of the VISION study are strictly in compliance with the International Conference on Harmonization (ICH) of Technical Requirements for Registration of Pharmaceuticals for Human Use Guideline for Good Clinical Practice (GCP), and the Helsinki Declaration of ethical principles [39,40].

## Discussion

The inability of monotherapies to act on the multiple pathophysiological mechanisms involved in T2DM and to maintain good glycemic control as a result of progressive deterioration of β-cell function provide the rationale for the early use of combination therapy with different classes of drugs [1,13]. As metformin lowers plasma glucose levels without affecting insulin secretion, the addition of an agent such as vildagliptin which has a stimulatory action on insulin secretion is a suitable choice for combination therapy in patients with T2DM [13,25,37]. Metformin has shown an incremental effect on levels of GLP-1 in obese subjects without diabetes via mechanisms other than DPP-IV inhibition [41,42]. An additive effect on levels of intact GLP-1 has also been reported in patients with T2DM receiving metformin and vildagliptin concomitantly as compared with drug-naïve patients receiving only vildagliptin [13], which further supports the use of this combination of drugs [41,42].

The efficacy and safety of metformin and vildagliptin combination therapy has been evaluated in several placebo-controlled and active-controlled trials. The addition of vildagliptin to a stable dose of metformin monotherapy has been shown to be effective in sustaining glycemic control for at least 1 year, and in improving β-cell function and reducing insulin resistance and inflammatory markers [43-47]. A recent study of vildagliptin/low-dose metformin combination therapy in treatment-naïve patients with T2DM showed superior glycemic control and favorable GI tolerability compared with high-dose metformin therapy. This suggests the potential of vildagliptin/metformin combination therapy in the management of T2DM [21]. A recent phase III study in patients with inadequate glycemic control on low-dose metformin (500 mg bid) demonstrated that the addition of vildagliptin 100 mg qd to low-dose metformin 500 mg bid resulted in a larger reduction in HbA1c as compared with up-titration of metformin therapy to 1000 mg bid. Moreover, the combination therapy was well tolerated without any increase in hypoglycemic events, and fewer GI events as compared with high-dose metformin monotherapy. Thus, early and more aggressive therapy in T2DM is more beneficial and can be considered in patients with poor glycemic control with metformin monotherapy [9].

In comparison with Caucasians, Asians have higher body fat at lower BMI levels and are thus more prone to obesity and related disorders such as diabetes mellitus, dyslipidemia, and hypertension at a lower BMI [48]. Consequently, in China, the BMI cut-offs for ‘overweight’ (24 kg/m^2^) and ‘obesity’ (28 kg/m^2^) are lower than those of the WHO criteria, and the population aged 60 years or more is defined as ‘elderly’ [49]. The VISION study will include Chinese patients with inadequate glycemic control (HbA1c 6.5%-9.0%), despite being on metformin monotherapy. The study will categorize patients into 4 subgroups according to their age and BMI. Patients in each group will be randomized to receive vildagliptin (50 mg bid) plus metformin (500 mg bid) or metformin (1000 mg bid) in a ratio of 5:1. As both obesity and age are independent risk factors for the development of T2DM and also influence the efficacy of any antidiabetic therapy, the VISION study will evaluate the efficacy and safety of the vildagliptin/metformin combination according to age and BMI in comparison with high-dose metformin.

## Conclusion

The VISION study aims to prove the efficacy and safety of early intensive combination therapy with vildagliptin and low-dose metformin in comparison with gradual upward titration of metformin therapy in Chinese T2DM patients who are inadequately controlled on low-dose metformin monotherapy. This report describes the rationale for and the design of the VISION study, the efficacy and safety results of which will be published when the study is completed. The key design elements and results of the study will also be communicated to public databases such as ClinicalTrials.gov.

## Abbreviations

AE: Adverse event; ANCOVA: Analysis of covariance; BMI: Body mass index; DPP-IV: Dipeptidyl peptidase IV; FAS: Full analysis set; FPG: Fasting plasma glucose; GI: Gastrointestinal; GIP: Glucose-dependent insulinotropic polypeptide; GLP-1: Glucagon-like peptide-1; HbA1c: Glycated hemoglobin; IDF: International Diabetes Federation; ITT: Intention-to-treat; LOCF: Last observation carried forward; PPG: Postprandial plasma glucose; PPS: Per-protocol set; SAS: Safety analysis set; T2DM: Type 2 diabetes mellitus; UKPDS: United Kingdom Prospective Diabetes Study; WHO: World Health Organization.
